Strong SCEDs can be characterized by three dimensions: (1) the design is divided into phases, (2) the design contains random assignment, and (3) the design should be replicated. Incorporating these dimensions improves the internal validity of the study and minimizes the possibility of history and maturation affecting the treatment effects [50]. These dimensions are incorporated into this study (Figures 1 and 2). First, the building blocks of a phase design can be divided into a baseline phase (A) and a treatment phase (B), with each phase containing multiple measurements. This can be made more complex by, for example, adding another treatment phase (C). Second, the phase design can be randomized by having different starting points for the treatment phase. In addition, a minimum of 3 measurement points is required per phase. In this study, randomization of the length of phases is used, which is increasingly considered important to make valid inferences about results. Third, the ways in which replication can occur is 2-fold: simultaneous replication entails conducting multiple phase designs at the same time, and sequential replication entails conducting multiple SCEDs to test the generalizability of the results. When both forms of replication are used, we speak of a hybrid design, which is called a nonconcurrent multiple baseline design, where partial temporal overlap is implied [50]. To adhere to these 3 dimensions and maximize internal validity, this study will use a nonconcurrent multiple baseline design.

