The multiple baseline SCED in this study is set up as shown in Figure 1. First, informed consent will be signed after families have received verbal and written information about the study. Second, participants will be dually randomized (by an external party) to determine their baseline period (4, 5, or 6 weeks of baseline measurements; phase A) and the addition of their VR element (VR at the start of CDI and after 3 or 6 sessions of CDI; phase B). After randomization, participants will start with phase A—the baseline period. Parents will electronically fill out the questionnaires weekly regarding child disruptive behaviors and parental stress using the ECBI and the short version of the OBVL. At the end of phase A, a pretreatment assessment will be performed. In this assessment, parents will be required to electronically fill out more questionnaires regarding both child and parental factors (Figure 1; see the *Assessment Instruments* section). In addition, the researcher will also make a video recording of the parent and child playing in 3 play situations (child-led play [CLP], parent-led play [PLP], and clean up [CU]), which will consequently be coded using the Dyadic Parent-Child Interaction Coding System (DPICS) [52]. Following this, in phase B, the intervention phase starts. Depending on their random allocation, families will start off with PCIT with or without the VR element. Once again, they will electronically fill out the ECBI and OBVL-*kort* (OBVL-K) weekly, and they will also register their homework completion and (if applicable) their VR completion sheets. During the PCIT sessions, PCIT therapists will register the parental progress weekly by coding 5 minutes of playtime with the DPICS. Once families reach CDI completion, they will move on to phase C, which is the parent-directed interaction (PDI) phase of PCIT. Measurements in phase C are identical to those in phase B. After treatment completion, a posttreatment assessment will be performed, which will be identical to the pretreatment assessment. Phase D is the follow-up assessment, which takes place 6 months after treatment completion. The assessment is also identical to the pre- and posttreatment assessments (Figure 2; 10 CDI sessions and 6 PDI sessions are used as a random example).

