### Assessment Instruments

The primary end point of positive parenting skills will be measured using the DPICS [52], and the added value of VR will be measured through VR assessments. Secondary end points, including the psychological functioning of the child, family dynamics and competences, and general therapy evaluation, will be measured through questionnaires and qualitative interviews. This is further explained in the following sections.

The DPICS [52] is a reliable and valid behavioral observational coding system designed to measure the quality of social interactions between parents and children. By coding open verbal and physical behaviors exhibited by both parents and children, the DPICS is able to assess the quality of the parent-child interaction as a construct. Behaviors that are coded are divided into the categories displayed in Textbox 1.

Parent and child behaviors as coded in the Dyadic Parent-Child Interaction Coding System.Parent behaviorsDirect command: compliance, noncompliance, and no opportunity to complyIndirect command: compliance, noncompliance, and no opportunity to complyQuestionBehavioral descriptionReflective statementLabeled praiseUnlabeled praiseNeutral talkNegative talkChild behaviorsNegative talkProsocial talkQuestionCommandWhineYell

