Coding during assessments will be done through 3 standard 5-minute play situations (CLP, PLP, and CU). Within the 5-minute observational videos, open verbal and physical behaviors will be scored on a score sheet. To progress within PCIT, parents must achieve 10-10-10 positive behaviors (10 behavioral descriptions, 10 reflective statements, and 10 labeled praises) and must display no negative leading behaviors (questions, negative talk, and commands in CDI) within the 5-minute observation time. At every assessment point during treatment, the therapist will score the parent during the 5-minute observation time with the DPICS. A video recording will be made of this, which will be used to assess the parents’ progression. In addition, an independent researcher will randomly select a few of the sessions’ video recordings and score the DPICS to assess the quality of the coding. Researchers will be trained beforehand to score the video recordings through DPICS and will be required to achieve an agreement rate of 80% on the scored behaviors. All observations will be transcribed verbatim to monitor interrater reliability and be subsequently double coded by an independent and reliable coder for 20% of the pretreatment, posttreatment, and follow-up treatment observations.

Further assessment instruments are divided into 4 subcategories and explained in the following sections.

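### The primary endpoint (DPICS) has one occasion in phase A, so the randomised baseline serves only the ECBI and OBVL-K, and within-case evidence for VR rests on families with a delayed VR start

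*Protocol article*

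**What the plan says.** Assessment Instruments names the outcome: "The primary end point of positive parenting skills will be measured using the DPICS". Study Design sets the general standard for the phases: "In addition, a minimum of 3 measurement points is required per phase". It says that phasing, random assignment and replication are all built into this trial.

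The same section describes two randomisations. One sets the baseline length ("4, 5, or 6 weeks of baseline measurements; phase A"). The other sets when VR is added: at the start of CDI, or after 3 or 6 CDI sessions.

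For phase A the weekly measures are listed: "Parents will electronically fill out the questionnaires weekly regarding child disruptive behaviors and parental stress using the ECBI" and the short OBVL. The DPICS enters through a separate visit: "At the end of phase A, a pretreatment assessment will be performed". At that visit the researcher films three play situations, which are then coded. Weekly DPICS coding is assigned to the therapists during PCIT sessions, in phases B and C. Assessment Instruments agrees, placing the therapist's scoring at the assessment points during treatment.

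The Conclusions subsection of the Discussion asserts that each participating family by itself supplies sufficient data for a meaningful statement about both the treatment and VR.

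**The concern.** A multiple-baseline design draws its strength from repeated measurement of the target outcome before the change, over baselines of randomly different length. Here the outcome with 4 to 6 baseline points is not the primary one. One DPICS occasion gives no baseline trend, no within-family variance and no effect of the randomised baseline length on the number of baseline points.

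Two conclusions are at stake. First, a rise in DPICS from phase A to phase B would be an uncontrolled before-after difference, however carefully the baseline length was randomised. Second, the trial's stated purpose is the added value of VR, so the comparator is PCIT without VR. Families given VR at the first CDI session never supply that comparator, yet the article counts every family as informative about VR.

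**Working it through.** **The plan's own figure.** The Participants section combines a minimum of 9 replicated cases with 40% attrition: 9 / (1 − 0.40) = 15. This reproduces the planned 15 families. It treats every one of the 9 completers as a replication.

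**Occasions in phase A** (Study Design, by randomised baseline length):

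| Baseline | ECBI | OBVL-K | DPICS | DPICS meets 3? |
|---|---|---|---|---|
| 4 weeks | 4 | 4 | 1 | no |
| 5 weeks | 5 | 5 | 1 | no |
| 6 weeks | 6 | 6 | 1 | no |

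The three play situations (child-led, parent-led, clean-up) are different tasks filmed on one occasion. They are not three repeated points.

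**DPICS before VR** (assuming each CDI session yields one coding; the 10-session CDI is the article's own illustrative example):

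| VR start | PCIT-only session codings | Pretreatment occasion | Coded CDI sessions left, if 10 in all |
|---|---|---|---|
| Start of CDI | 0 | 1 | 10 |
| After 3 sessions | 3 | 1 | 7 |
| After 6 sessions | 6 | 1 | 4 |

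The pretreatment occasion is not simply one more point in the session series. The researcher films it over three situations, whereas the therapist codes 5 minutes of play in session.

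**Families able to show VR's added value on DPICS within the case.** The allocation ratio is not stated. If it is equal across the three VR starts, 15 / 3 = 5 families have VR from the start, and 15 − 5 = 10 have at least 3 PCIT-only points. If 40% of those 10 also left before giving usable data under VR, 10 × (1 − 0.40) = 6 would remain. The range is thus 6 to 10, against the 9 replications that the Participants section cites.

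**The case against.** The best defence is that phase A is not the comparator that matters. The objective is what VR adds to PCIT, and PCIT itself is already well studied. The second randomisation staggers VR inside phase B, where DPICS is coded weekly. Families starting VR after 3 or 6 sessions have about 3 or 6 PCIT-only points, enough for a 3-point minimum. More DPICS in phase A would not separate VR from PCIT in any family. All of this stands. A reader might infer that the primary endpoint has no multiple baseline and no stagger anywhere; the documents do not support that.

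A reader might also infer that the article expressly claims the 3-point minimum is met for DPICS. It does not. The sentence is general and names no outcome, and phase A does hold 4 to 6 weekly questionnaire occasions. The shortfall appears only when the general rule is set beside the DPICS schedule.

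It can further be said that the condensed Statistical Analysis section gives no primary model, so how the baseline length would enter it cannot be known. That is fair, and no claim is made here about the model. But the measurement schedule is stated measure by measure and phase by phase, and no analysis plan can supply baseline observations that were not collected. The missing figure does not change this, because the text is explicit.

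None of these arguments rescues the families with VR from the start.

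**Conclusion.** The point holds for phase A and for families with VR from the start of CDI. DPICS has 1 phase A occasion in every family, against a stated minimum of 3, so the randomised 4-, 5- or 6-week baseline is a multiple baseline for the ECBI and OBVL-K only. For DPICS, the staggered contrast is PCIT alone versus PCIT-VR within CDI, in families with a delayed VR start. Families with VR from the start have a single earlier DPICS occasion and begin PCIT and VR together. They cannot show VR's added value on the primary endpoint within the case, contrary to the Conclusions subsection.

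On equal allocation, about 10 of 15 families can count as within-case replications. The lower figure of 6 further assumes that the planned attrition falls evenly and before usable data under VR. The phase A count needs no assumption.

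The article does not say that a phase A to phase B change in DPICS will be reported as SCED evidence. As written, it simply leaves that reading open.

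**What to change.** State in Study Design and Statistical Analysis that:

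- (a) phase A and its randomised length support SCED inference on the ECBI and OBVL-K only;
- (b) the primary SCED contrast on DPICS is PCIT alone versus PCIT-VR across the coded CDI sessions around the randomised VR start;
- (c) families with VR from the start contribute to DPICS only through comparison between families or as pre-post description, and are not counted as within-case replications of the VR effect;
- (d) the pretreatment DPICS is a pre-post value or a covariate, and a phase A to phase B change in DPICS is not presented as SCED evidence.

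Qualify the 3-point sentence in Study Design by outcome, and the claim about every family in Conclusions.

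The cost is wording. No visit, measure or change to N is needed. The price is in the claim: fewer families count as replications on the primary endpoint, about 10 of 15 if allocation is equal. Extra DPICS recordings in phase A are not proposed. They would add a procedure, could not be obtained from families already past baseline, and would not isolate VR from PCIT.

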**Figure 1 figure1:**
[figure not shown]
Graphical view with information per phase. AISI: Attachment Insecurity Screening Inventory; ASR: Adult Self-Report; CAPI: Child Abuse Potential Inventory; CDI: child-directed interaction; CLP: child-led play; CU: clean up; DPICS: Dyadic Parent-Child Interaction Coding System; ECBI: Eyberg Child Behavior Inventory; KJTS: Kind en Jeugd Trauma Screener; OBVL: opvoedingsbelasting vragenlijst; OBVL-K: opvoedingsbelasting vragenlijst-kort; PCIT: Parent-Child Interaction Therapy; PDI: parent-directed interaction; PLP: parent-led play; TAI: Therapy Attitude Inventory; VR: virtual reality.

**Figure 2 figure2:**
[figure not shown]
Three separate examples of the multiple baseline single-case experimental design in phases (using a fictitious number of allocated sessions).

### Treatment

PCIT focuses on changing dysfunctional parent-child interactions in 2 phases and teaches authoritative parenting [17], which implies firm control, warmth to the parent-child relationship, and a balance between discipline and stimulating independence [53]. Therapists coach parents from behind a 1-way screen through an earpiece [17]. In the first phase of PCIT, which is the CDI phase, emphasis is placed on building up the quality of the parent-child relationship and increasing positive parenting skills. In addition, in this phase, children begin to build the ability to regulate their behavior [15]. This first phase lays the foundation for effective behavior change. In the CDI phase, parents follow their child’s lead in playing and are coached on using positive parenting skills, specifically, praise, reflective statements, behavioral descriptions, imitation, and enthusiasm [17]. The number of CDI sessions is dependent on the parents meeting the skill criteria (10 behavioral descriptions; 10 reflective statements; 10 labeled praises; and <3 questions, commands, or negative verbalizations during a 5-minute observation period).

However, the CDI phase alone is typically insufficient for children with disruptive behavior to return to displaying normal behavior [54]. After meeting the CDI skill criteria, the second phase of PCIT, which is the PDI, starts. The goal of the PDI phase is to further enhance the parents’ positive parenting skills to set consistent, predictable, and age-appropriate boundaries for their children [17]. In the PDI phase, parents are coached on using clear commands and how to apply consequences for compliance (praise) and noncompliance (timeout). In addition, they are taught and encouraged to keep using the positive parenting skills from the first phase. Once parents demonstrate achievement of skill criteria of both CDI and PDI skills, and their children’s behaviors according to the raw score on the ECBI Intensity Scale is <114, the treatment is completed, as standard protocol dictates [17].

In October 2020, 12 therapists were trained to become PCIT therapists at a clinical treatment center in the Netherlands. They were trained by PCIT International certified trainers, thus ensuring the quality of treatment. Therapists follow PCIT protocol and have biweekly consultations with their trainers to keep track of their progress. In addition, the clinical center already had multiple PCIT therapists trained approximately 10 years ago, who also still provide PCIT to families. Both newly trained and other PCIT therapists will help collect data for this study.

### VR Implementation

In the standard protocol of PCIT, parents are required to practice the skills taught throughout the sessions in *special time* at home with their children. This means that the families participating in PCIT have homework to do at home to improve weekly. This study suggests that parents also practice the skills they are taught in the sessions at home in the virtual environment that will be created for them. As such, the implementation of VR is an additional element to the standard PCIT protocol PCIT, as described previously.

There are multiple different systems within VR, one of which is a head-mounted display [30]. This study will be using 360° videos that can be played on a smartphone device placed on the head-mounted display. As a result, the person with the headset on can look around 360° from a singular point in the virtual environment, meaning that the environment does not change if the person wearing the headset decides to move. In technical terms, this is referred to as having 3 df. This option of technology was chosen as opposed to other forms of VR as it is inexpensive and easy to use through a simple (but protected) link, thus allowing people to access it from anywhere and at their own time, which increases accessibility and applicability.

The 360° video content for this study will be recorded using child actors for different scenarios. The various scenarios depict the positive parenting skills that are taught in the CDI phase (praise, behavioral description, reflective statement, and ignoring unwanted behavior), thus allowing parents to repeatedly practice these skills in the comfort of their own home. These verbalizations provide a variety of responses and depict scenarios with commonly used toys. As there are multiple scenarios with which the parent can practice, parents are free to choose the scenarios that most suit their goal of practice.

The recorded video will be edited into fragments containing key events that call for a response from the parent by answering a multiple-choice question asked at the end of each fragment. The fragments are assembled into a therapy scenario using a web-based scenario editor in which therapy is described by a nonlinear sequence of fragments, the order of which is determined by a parent’s responses. Coaching—in the way that the therapist would do in therapy sessions—is implemented by providing textual feedback to each given answer. The technology to support PCIT-VR is based on a web-based design that (1) provides a VR scenario editor, (2) functions as a server that delivers the content of a therapy scenario to the parent’s headset, and (3) records performance data for future analysis. The web-based design allows the therapy scenarios to be used on any device that runs on a web browser and allows use from any location with internet access.

### Assessment Instruments

The primary end point of positive parenting skills will be measured using the DPICS [52], and the added value of VR will be measured through VR assessments. Secondary end points, including the psychological functioning of the child, family dynamics and competences, and general therapy evaluation, will be measured through questionnaires and qualitative interviews. This is further explained in the following sections.

The DPICS [52] is a reliable and valid behavioral observational coding system designed to measure the quality of social interactions between parents and children. By coding open verbal and physical behaviors exhibited by both parents and children, the DPICS is able to assess the quality of the parent-child interaction as a construct. Behaviors that are coded are divided into the categories displayed in Textbox 1.

Parent and child behaviors as coded in the Dyadic Parent-Child Interaction Coding System.Parent behaviorsDirect command: compliance, noncompliance, and no opportunity to complyIndirect command: compliance, noncompliance, and no opportunity to complyQuestionBehavioral descriptionReflective statementLabeled praiseUnlabeled praiseNeutral talkNegative talkChild behaviorsNegative talkProsocial talkQuestionCommandWhineYell

Coding during assessments will be done through 3 standard 5-minute play situations (CLP, PLP, and CU). Within the 5-minute observational videos, open verbal and physical behaviors will be scored on a score sheet. To progress within PCIT, parents must achieve 10-10-10 positive behaviors (10 behavioral descriptions, 10 reflective statements, and 10 labeled praises) and must display no negative leading behaviors (questions, negative talk, and commands in CDI) within the 5-minute observation time. At every assessment point during treatment, the therapist will score the parent during the 5-minute observation time with the DPICS. A video recording will be made of this, which will be used to assess the parents’ progression. In addition, an independent researcher will randomly select a few of the sessions’ video recordings and score the DPICS to assess the quality of the coding. Researchers will be trained beforehand to score the video recordings through DPICS and will be required to achieve an agreement rate of 80% on the scored behaviors. All observations will be transcribed verbatim to monitor interrater reliability and be subsequently double coded by an independent and reliable coder for 20% of the pretreatment, posttreatment, and follow-up treatment observations.

Further assessment instruments are divided into 4 subcategories and explained in the following sections.

### VR Evaluation

#### VR User Analytics

Each parent will have a personal sign-in that registers their answers when using VR. Their progress will be monitored any time they log in and use a therapy scenario.

#### VR Completion

The parents will be required to use a VR tracking sheet, where they will fill out the number of days that they had completed the VR training. This will then be divided by the total number of days in the week, yielding a percentage of VR completion per week. Parents will be required to fill this out weekly (alongside their *special time homework completion*, which is incorporated in the standard protocol of PCIT) as soon as they receive VR.

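### Weekly VR completion is scored from parent self-report alone, although the web system identifies each parent and monitors each use of a scenario

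*Protocol article*

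**What the plan says.** Under *VR Evaluation*, the article lists two measures of use, one after the other, and a parent interview.

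- **VR User Analytics.** "Each parent will have a personal sign-in that registers their answers when using VR". The section adds: "Their progress will be monitored any time they log in and use a therapy scenario".
- **VR Completion.** The input is a tracking sheet on which parents report their own use: "they will fill out the number of days that they had completed the VR training". The score is then fixed: "This will then be divided by the total number of days in the week, yielding a percentage of VR completion per week". On timing, "Parents will be required to fill this out weekly", starting when they receive VR and next to the special-time homework record.

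The *VR Implementation* section describes a web-based system that serves scenarios to the headset and "records performance data for future analysis".

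Two other places show what the measure is for. *Aims* includes the evaluation of parents' compliance with VR among the secondary objectives. *Assessment Instruments* says that the added value of VR will be measured through the VR assessments as a group, and names observed parenting skills, coded with the Dyadic Parent-Child Interaction Coding System (DPICS), as the primary end point.

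The article does not say which of the two measures of use serves the compliance objective, or that one will be checked against the other.

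**The concern.** The completion percentage is a stated scoring rule, not a detail left open, and its only input is the parents' own count. A weekly count of days depends on recall. It is also returned together with the homework record in a treatment where practice is expected, so some reporting in the desired direction is plausible. Meanwhile the scenarios are delivered by a system that identifies the parent and monitors use, which should be less exposed to both problems.

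If parents over-report, compliance will look better than it was. A family that used VR little could then be read as one that used it well without benefit. The rationale in *Aims* is that skills will be trained more often with VR, and days of use per week is the planned measure closest to that frequency. It is therefore worth measuring as well as the existing data allow.

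The denominator raises a smaller, related matter. It is every day of the week, whether or not VR was usable on that day. The *Discussion* names the functioning of the application on different smartphones as a potential problem.

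**Working it through.** **No stated figure to reproduce.** The article gives no number for VR completion, for its error or for any analysis that uses it. The check applies the article's own formula.

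**Inputs**

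- Numerator: days reported by the parent (*VR Completion*).
- Denominator: days in the week, 7 (*VR Completion*).
- Second source: per-parent sign-in and monitoring of each use (*VR User Analytics*, *VR Implementation*).

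**Formula.** Completion (%) = 100 × reported days / 7.

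**Sensitivity to a misreported day.** One day changes the score by 100 × 1/7 = 14.3 percentage points. The scenarios below are illustrations, not estimates:

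| True days | True score | Reported one day too many | Reported two days too many |
|---|---|---|---|
| 3 | 42.9% | 57.1% | 71.4% |
| 4 | 57.1% | 71.4% | 85.7% |
| 5 | 71.4% | 85.7% | 100% |

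**Effect of the denominator.** Suppose that the application fails on two days of a week and the parent uses it on the other five. The formula gives 100 × 5/7 = 71.4%. Over the days on which VR was available the figure is 100 × 5/5 = 100%. The formula cannot tell a day not attempted from a day not possible.

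**Random error, by assumption only.** Let true days per week have SD 2, and let the reporting error have SD 0.5 to 2 days. Neither value is in the article. Reliability = SD²(true) / [SD²(true) + SD²(error)]:

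- error SD 0.5: 4 / 4.25 = 0.94
- error SD 1: 4 / 5 = 0.80
- error SD 1.5: 4 / 6.25 = 0.64
- error SD 2: 4 / 8 = 0.50

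The range is wide because the inputs are unknown. It also describes random error only. A constant over-report raises the level of apparent compliance but, short of the 100% ceiling, does not flatten a slope.

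**What is not touched.** The count of 15 families in *Participants* agrees with 9 / (1 − 0.40) = 15, which has no term for VR use. The randomisation in *Study Design* sets the baseline length and the timing of VR introduction, neither of which depends on the sheet. DPICS is coded from observation.

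**The case against.** The strongest reply is that nothing is lost. The analytics are a separate, listed measure, so an electronic record of use is already in the plan. The article nowhere says that the sheet alone will serve the compliance objective; that choice may sit in a fuller protocol or analysis plan that is not shown. All of this stands, and it limits the point to how the completion percentage is scored.

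Two stronger readings are tempting. A reader might infer that the sheet is the trial's measure of VR dose and that its error would weaken an estimated dose-response; with reliability assumed at 0.5 to 0.8, a regression slope would shrink by 20% to 50%. The article does not support this. It gives VR completion no such role, it plans no regression of skill gain on completion, and the reliabilities are assumed.

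A reader might also infer that a complete, objective log of the same quantity exists and is being ignored. That goes too far as well. The article mentions answers, progress and performance data, but not dated sessions or a marker for a completed training. It describes the technology as still being developed and names technical failure as a risk, so a parallel sheet is a reasonable safeguard. The sheet also gives VR and special time matching weekly records, which a log-only definition would lose.

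What the reply does not remove is that the percentage called completion is fixed on self-report alone, with no use of the electronic record.

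**Conclusion.** The point holds as an improvement to a secondary process measure. VR completion is scored from the weaker of two sources already being collected, and compliance with VR is a stated secondary objective. The size that follows from the article is 14.3 percentage points of weekly completion per misreported day. The direction and amount of actual misreporting are unknown.

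This rests on one assumption: that the log stores session dates, or can be made to, so that days of use can be counted. The article does not say so.

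It would be wrong to conclude that the primary end point, the randomised comparison or the sample size is compromised, or that a planned dose-response estimate is biased. The documents describe no such estimate, and the other three do not depend on the sheet.

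**What to change.** First confirm that the log stores the date of each session for each parent. Then redefine the score in *VR Completion* along these lines:

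- **Numerator:** days in the week with logged scenario use. Because the path through a scenario depends on the parent's answers, state a rule for what counts as completed that suits branching scenarios.
- **Denominator:** days in that week on which VR was available to the parent.
- **Tracking sheet:** keep it as a supplementary measure and as backup for weeks in which technical failure leaves the log incomplete. Mark the weeks scored that way.
- **Reporting:** give the agreement between sheet and log.

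Parents would have nothing new to fill in. The cost is a revised definition, an export of the log and modest data processing. The drawback is dependence on the completeness of the log while the application is still being developed, which is the reason for keeping the sheet.
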